### Safety Monitoring and Reporting

Safety oversight for the study will be carried out under the direction of the independent safety monitor working within the framework of the Data and Safety Monitoring Board Charter to ensure an objective assessment of the safety and efficacy of the study. AEs deemed secondary to the administration of the pessary will be monitored and reported accordingly by either the investigators or the independent safety monitor, from administration to the end of follow-up. Relevant physical examinations or investigations will then be carried out to ensure the effects of the AE are managed accordingly. The primary investigator will record the AE appropriately into the patient’s medical record or study shadow file.

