### Participants

The study population will consist of 20 women undertaking FET cycles at the Public Fertility Care of The Royal Women’s Hospital (RWH), Melbourne, Australia. The recruitment process will commence at this location, whereby clinicians and nursing teams will be invited to screen the patients they interact with for eligibility for the study. These staff members will be trained on appropriate screening according to the study protocol and will be delegated by the principal investigator. Eligible patients will then be approached for study by team members who are not directly involved in potential participants’ clinical care and, therefore, will not have had any clinical interactions with the participant. All patients will be provided with a patient informed consent form (Multimedia Appendix 1) to ensure they are familiar with the protocol requirements and understand their rights as participants. Additionally, they will be provided with a patient information document created by the research team (Multimedia Appendix 2) to assist with patient education surrounding the use of the P4 pessary during the study.

Inclusion criteria consist of women with regular cycles defined as 21-35 days, women younger than 40 years at the start of a cycle, and women whose BMI ranges from 18 to 35, inclusively.

The exclusion criteria include anovulatory women, women who are 40 years or older at the start of the cycle, and women who have preexisting contraindications to exogenous P4 supplementation, such as those with liver disease or thromboembolic disease. The exclusion criteria will also include the use of additional LPS (eg, subcutaneous), women with uterine pathology, including congenital malformations of the female reproductive tract, endometrial polyps, intrauterine adhesions, adenomyosis, and leiomyoma. Regarding the retrospective element of the study, patients for whom inclusion criteria information is lacking will not be included in the study.

The control group will consist of retrospective data from 20 women, matched against inclusion and exclusion criteria, within the Public Fertility Services of the RWH data bank. These controls would have undergone tNFET at the service provider within the preceding 12 months of the study start date.

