### Outcome Measures

The primary outcome will be the presence of corpus luteum with a characteristic “ring of fire” appearance on the transabdominal ultrasound on the day of embryo transfer.

The secondary outcomes consist of the number of clinic visits required per patient undergoing this protocol, the biochemical pregnancy rate defined as the detection of βhCG in serum or urine [14], and the clinical pregnancy rate defined as the ultrasonographic visualization of one or more gestational sacs [14].

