### Randomization

This is a pilot prospective cohort study without randomization.

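### As worded, adverse event monitoring and reporting is conditional on attribution to the pessary, so harms arising from the new timing have no stated route into the safety data

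*Protocol article*

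**What the plan says.** All of the safety text is in the protocol article under Safety Monitoring and Reporting. Oversight is by an independent safety monitor under a Data and Safety Monitoring Board charter, with the stated purpose "to ensure an objective assessment of the safety and efficacy of the study". The capture rule follows: "AEs deemed secondary to the administration of the pessary will be monitored and reported accordingly", and this is done "by either the investigators or the independent safety monitor, from administration to the end of follow-up". Examinations or investigations then follow for the event in question, and the section closes: "The primary investigator will record the AE appropriately into the patient’s medical record or study shadow file".

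The relevant context is elsewhere in Methods:

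- Randomization: "This is a pilot prospective cohort study without randomization".
- Participants: "The study population will consist of 20 women undertaking FET cycles", and "The control group will consist of retrospective data from 20 women, matched against inclusion and exclusion criteria".
- Outcome Measures: the primary outcome is a corpus luteum on ultrasound on the day of transfer. "The secondary outcomes consist of the number of clinic visits required per patient undergoing this protocol, the biochemical pregnancy rate", followed by the clinical pregnancy rate. No AE, ectopic pregnancy or pregnancy-loss outcome is listed.
- Intervention and Control: both groups receive the same brand of vaginal progesterone pessary. In the intervention it starts while serum progesterone is below 5 nmol/L, and transfer is timed from that start. In the control it starts after ovulation (defined as progesterone above 5 nmol/L), and transfer is timed from the LH surge.

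**The concern.** A causal judgement is normally made about an AE after it has been recorded, so that it can be checked and, if necessary, revised. Here the judgement stands in front of monitoring and reporting. An event judged unrelated leaves no stated trace, so the judgement cannot be audited.

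The filter also refers to the product rather than to the strategy under test. The pessary is common to both groups; the new element is starting progesterone before ovulation is confirmed and scheduling transfer from that point. A harm arising from that timing could reasonably be judged not to be due to the pessary.

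The article itself treats such outcomes as important. The Introduction cites miscarriage and obstetric complications as drawbacks of artificial cycles, and cites miscarriage and live birth when it argues that the new approach gives comparable results. What is at stake is whether the pilot's safety description covers the new protocol or only the pessary.

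**Working it through.** **Step 1: is there another route for an AE not attributed to the pessary?** The sentence on examinations and the sentence on recording both refer back to the AE of the capture rule. Outcome Measures lists no safety outcome. The remaining sections contain no rule for AE collection. As published, there is no other route.

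**Step 2: which events do the listed outcomes already capture?** Serum hCG is taken 10 days after transfer, and women who test positive have a scan at 6-7 weeks.

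- Loss between the hCG test and the scan: visible as biochemical without clinical pregnancy, whatever its cause.
- Ectopic pregnancy: not identifiable as such from either pregnancy rate.
- Loss after the scan: already counted as a clinical pregnancy, and no later outcome is listed, although follow-up can run up to 12 weeks.
- Any other AE not attributed to the pessary: not captured.

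The gap is therefore the last three items.

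**Step 3: size.** The article gives no AE rate and no attribution share, so there is no figure to reproduce. The following is an illustration only.

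Inputs: n = 20 (Participants), assuming that all 20 start progesterone; p = true proportion of women with an event (assumed 5%, 10%, 20%); f = share of such events attributed to the pessary and so reported (assumed 1, 0.5, 0.25).

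Formula: chance of recording no event = (1 − p·f)^20; expected number recorded = 20·p·f.

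At p = 10%:

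- f = 1: 0.90^20 = 0.122; expected 2.0
- f = 0.5: 0.95^20 = 0.358; expected 1.0
- f = 0.25: 0.975^20 = 0.603; expected 0.5

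Chance of recording no event over the assumed range:

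| True rate p | f = 1 | f = 0.5 | f = 0.25 |
|---|---|---|---|
| 5% | 35.8% | 60.3% | 77.8% |
| 10% | 12.2% | 35.8% | 60.3% |
| 20% | 1.2% | 12.2% | 35.8% |

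The direction does not depend on the assumed values: for any f below 1 the expected recorded count falls in proportion to f.

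**The case against.** The strongest case on the other side is that the article condenses a longer protocol and refers to a safety charter that is not shown. All-cause logging and causality grading could well be in those documents, and the word *only* does not appear in the sentence. That is right as far as it goes. The point is therefore about what the published sentence fixes, and cannot be a claim that other events will certainly be discarded. It still stands, because the article states a rule and makes attribution its condition.

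Several stronger readings are tempting but not supported:

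- *Unblinded investigators alone decide what is recorded.* The text does not say who makes the attribution, and it names the independent safety monitor as a possible monitor and reporter. Lack of blinding is a fair inference from an open, non-randomized design, but it is not stated. The monitor is a partial safeguard; the same attribution condition applies to either party.
- *Early pregnancy loss goes unseen.* Loss before the 6-7 week scan can be read from the two pregnancy rates, which are collected regardless of cause.
- *Cancelled cycles are missed harms.* Cancellation is a process outcome and not ordinarily an AE.
- *A finding of no AEs will justify the later trial.* The Implications section ties progression to the corpus luteum, not to AE counts. The remark that no AEs were reported concerns an earlier series of 42 participants.
- *The upper confidence limit for 0 of 20 measures the defect.* The exact two-sided 95% limit, 1 − 0.025^(1/20) = 16.8%, follows from n = 20 alone and would be the same after the fix.

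It can also be said that a 20-woman feasibility pilot without a safety endpoint needs no elaborate safety apparatus. That limits the weight of the point, but the remedy is small in proportion.

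**Conclusion.** The point holds in a limited form. As published, attribution to the pessary is the condition for monitoring and reporting an AE, and no other part of the article provides for collection regardless of cause. Because controls also receive a pessary and the novelty lies in timing, ectopic pregnancy, pregnancy loss after the 6-7 week scan and any other AE not attributed to the pessary have no stated route into the safety data. This weakens the objective assessment that the section promises. The primary outcome and the listed secondary outcomes are unaffected.

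The extent of under-recording is unknown. The rise in the chance of recording no event at a 10% true rate, from 12% to 36% or 60%, rests entirely on the assumed rate and attribution shares and on all 20 women starting progesterone. Only the direction follows from the rule. This is an inexpensive improvement worth making, not a defect that undermines the study.

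**What to change.** Reword the capture sentence so that all AEs from the first dose of study progesterone to the end of follow-up are recorded regardless of cause, naming ectopic pregnancy and pregnancy loss explicitly. Make seriousness and relatedness recorded fields, completed after the event is logged, and make all events available to the independent safety monitor. In the report, show all AEs and related AEs separately, each out of all women who received study progesterone.

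The cost is one changed sentence, the added fields on the AE record and a modest increase in events logged. No treatment, visit or outcome changes. If the full protocol or the safety charter already works this way, only the published sentence needs correcting.

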### Integration and Dissemination of Findings

On completion of the study, primary and secondary outcomes will be disseminated to investigators, ensuring the confidentiality of patient information. Findings will be synthesized and communicated to colleagues of the RWH RSU and Human Research Ethics Committee, as well as in further peer-reviewed publications related to the RCT that may be conducted following the completion of this cohort study. Additionally, findings will be communicated confidentially in potential presentations at national and international conferences.

## Results

This project was conceived in November 2023. It was subsequently approved by the RWH Human Research Ethics Committee on July 17, 2024. Local governance approval was granted on August 28, 2024.

Commencement of the study began in September 2024, aiming for a duration of completion of 9 months, and completion of follow-up and submission of the study for publication in September 2025.

## Discussion

### Overview

We have designed a pilot cohort nonrandomized study to assess the feasibility of a novel P4mNFET protocol that circumvents the need to monitor for an endogenous LH surge to pinpoint ovulation to schedule FET. This protocol, therefore, may combine the advantages of the tNFET, AFET, and mNFET into one protocol that provides greater flexibility for the timing of transfer with fewer requirements for surveillance and no impact on pregnancy outcomes.

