## Methods

### Study Type

The proposed study will adopt a pilot cohort methodology consisting of 12 weeks of intervention and follow-up monitoring of participants for primary and secondary outcomes. Secondary outcomes will be compared with retrospective data from the tNFET control group.

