### Statistical Analysis and Sample Size

Given the qualitative and binary nature of the primary outcome, no statistical testing is proposed for this. Secondary outcomes will undergo *t* tests and Mann-Whitney *U* tests for data that are normally and not normally distributed, respectively. Should there be significant variation in the key baseline variables between the study and the control group, a multivariate analysis will be performed.

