### Implications

The implications of this study are that it may inform the future of FET. If primary outcomes are met such that the presence of the corpus luteum is maintained with P4mNFET, then a noninferiority RCT will be carried out to formally compare the two methods. Moving forward, this P4mNFET protocol may provide clinics the opportunity to perform FET with greater scheduling flexibility and comparable outcomes to established methods while potentially leading to cost-saving and increased efficiency.

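### With 20 women per group and difference tests only, a non-significant pregnancy comparison in this pilot cannot support the hoped-for comparable outcomes

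*Protocol article*

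**What the plan says.** The Participants section sets both group sizes: "The study population will consist of 20 women undertaking FET cycles", and "The control group will consist of retrospective data from 20 women". Study Type states that "Secondary outcomes will be compared with retrospective data from the tNFET control group". Outcome Measures lists the secondary outcomes as number of clinic visits, biochemical pregnancy rate and clinical pregnancy rate; the last two are binary for each woman.

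Statistical Analysis and Sample Size says of the primary outcome, a corpus luteum on the day of transfer, that "no statistical testing is proposed for this". For the secondary outcomes it names t tests and Mann-Whitney U tests "for data that are normally and not normally distributed, respectively", with a multivariate analysis if key baseline variables differ significantly. It gives no significance level, power, effect size or margin for this pilot.

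Two Discussion passages look ahead to the pregnancy result. Overview says the protocol may combine the advantages of existing methods, with "greater flexibility for the timing of transfer with fewer requirements for surveillance and no impact on pregnancy outcomes". Implications says it may let clinics perform transfers with "greater scheduling flexibility and comparable outcomes to established methods". In both places the word may stands before the quoted words. Limitations names the weaker rigour of a cohort design and data entry in the retrospective controls. It does not mention sample size or imprecision.

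**The concern.** The stated analysis and the Discussion language do not fit together. A t or Mann-Whitney test asks whether the groups differ. Phrases such as no impact or comparable outcomes ask whether they are close enough. The article attaches no margin, interval or limit on interpretation to the pilot's comparison. Within the pilot, the only result of the named tests that could seem to bear out those phrases is a non-significant one. With 20 per group, that result is likely whether or not the new protocol lowers pregnancy rates.

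What is at stake is how the pilot's own report will be read. It is due for publication before any randomised trial could report. A non-significant p-value beside the words comparable outcomes could be taken as reassurance while the data remain compatible with a large loss of pregnancies.

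**Working it through.** The article contains no power or sample-size derivation, so there is no figure of its own to reproduce. The check asks how often the named tests would miss a real fall.

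**Inputs from the article**
- 20 women per group (Participants).
- Difference tests, t or Mann-Whitney (Statistical Analysis and Sample Size).

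**Assumptions, because the article gives no figure**
- Two-sided 5% level.
- Independent groups, with all 20 women per group analysed.
- Control pregnancy rate of 30%, 40% or 50%, with 60% as a favourable extreme.

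**Method.** Let X be pregnancies among P4mNFET women, binomial (20, p1), and Y those among controls, binomial (20, p0). Each of the 21 × 21 possible tables is tested.

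Miss rate = 1 − Σ P(X = x) P(Y = y), summed over tables with p ≤ 0.05.

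The Mann-Whitney test is the asymptotic version with tie and continuity corrections. Fisher's exact test is not planned and is shown only for reference.

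**Missing a halving of the rate**

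| Control → P4mNFET | t test | Mann-Whitney | Fisher (not planned) |
|---|---|---|---|
| 30% → 15% | 80% | 80% | 88% |
| 40% → 20% | 71% | 73% | 81% |
| 50% → 25% | 63% | 66% | 73% |
| 60% → 30% | 54% | 55% | 65% |

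**Missing a 10-point fall**

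| Control → P4mNFET | t test | Mann-Whitney |
|---|---|---|
| 30% → 20% | 89% | 89% |
| 40% → 30% | 90% | 91% |
| 50% → 40% | 91% | 92% |

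With no true difference, the same two tests are non-significant about 95% to 96% of the time at these control rates. Seeing non-significance therefore hardly separates no effect (95% to 96%) from a 10-point loss (89% to 92%).

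**What an interval would show.** Newcombe's method combines the Wilson limits (l, u) of the two proportions. With d = p1 − p0:
- lower limit = d − √[(p1 − l1)² + (u0 − p0)²]
- upper limit = d + √[(u1 − p1)² + (p0 − l0)²]

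*Identical results, 8/20 v 8/20.* The Wilson limits for 8/20 are 0.219 and 0.613. The half-width is √[(0.400 − 0.219)² + (0.613 − 0.400)²] = 0.280, so the 95% CI runs from −28 to +28 points.

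*3/20 v 8/20.* The Wilson limits for 3/20 are 0.052 and 0.360, and d = −0.25.
- Lower: −0.25 − √[(0.150 − 0.052)² + (0.613 − 0.400)²] = −0.485.
- Upper: −0.25 + √[(0.360 − 0.150)² + (0.400 − 0.219)²] = +0.028.

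This observed fall of 25 points is non-significant under both named tests (t p = 0.08, Mann-Whitney p = 0.08). Its interval, about −48 to +3 points, shows at once that it is no evidence of comparability.

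**Scale.** By the usual normal-approximation formula, 80% power to detect a halving would need about 121, 82 and 58 women per group at control rates of 30%, 40% and 50%.

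**The case against.** The strongest reply is that the article never claims equivalence from this pilot, and much of that stands.

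- **Hedging.** A reader who starts at the quoted words might infer that the study intends to conclude there is no effect on pregnancy. The full sentences in Overview and Implications are both governed by may. The stated aim is feasibility, and pregnancy rates are secondary outcomes.
- **Other grounds for the expectation.** A reader might also infer that comparability would rest only on these 20 v 20 tests. The documents do not support that. The Introduction bases the expectation on earlier cohort studies. The Abstract, Introduction, Limitations and Implications all point to a noninferiority trial for the comparison.
- **Progression.** Implications ties the move to that trial to the corpus luteum result. No pregnancy p-value serves as a gate.
- **Missing margin.** A noninferiority margin belongs to the later trial, and its absence from a feasibility pilot is not an error.
- **Detail left elsewhere.** An article may leave interval methods to a fuller plan. That answers a complaint that an interval is missing. It does not fully answer this point, because the article does state its analysis for the secondary outcomes, and what it states is a difference test for binary rates.

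The figures also depend on assumed control rates. At 60% the named tests miss a halving only slightly more often than not, so it would be wrong to call a non-significant result close to guaranteed for an effect of that size.

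What remains is narrower. The pilot plans and will publish its own pregnancy comparison, uses optimistic if hedged language about it, and does not list imprecision among its limitations.

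**Conclusion.** The point holds as one about analysis and interpretation within the pilot. Under the named tests, with assumed control rates of 30% to 50%, a two-sided 5% level and 20 analysed per group, a halving of the pregnancy rate is missed about 63% to 80% of the time (54% to 55% at a 60% control rate). A 10-point fall is missed about 89% to 92% of the time. A non-significant result therefore says almost nothing about comparability, and even identical observed rates of 8/20 leave an interval of about ±28 points.

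The feasibility aim, the primary outcome and the decision to proceed to the noninferiority trial are untouched. The documents do not show a plan to declare equivalence, and the finding should not be read as saying so.

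**What to change.** 1. **Statistical Analysis and Sample Size.** Replace the t or Mann-Whitney test for biochemical and clinical pregnancy with the difference in proportions (P4mNFET minus tNFET) and its two-sided 95% CI, for example by Newcombe's method. Add that a non-significant difference will not be read as evidence of comparable outcomes. The named tests can stay for the number of clinic visits.
2. **Overview, Limitations and Implications.** State that with 20 women per group the pilot cannot establish comparable pregnancy outcomes, and that this question is left to the planned noninferiority trial. In Limitations, name small size and imprecision alongside the two limitations already given.

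The cost is a few sentences and one interval per pregnancy outcome, with no extra patients, visits or procedures. The downside is a more modest claim from the pilot. An interval shows imprecision only; it does not remove bias from using retrospective, non-randomised controls.

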### Anticipated Challenges

As with any study of this kind, some challenges are anticipated with patient recruitment. The research team aims to mitigate this via appropriate counseling and use of our patient informed consent form, which is in a question-and-answer format.

The second challenge may be the accuracy of the retrospective data for the control group. This is an inherent issue with all retrospective studies. However, it is anticipated that key secondary outcomes will be accurately reported.

